# ASSESSMENTS AND PROCEDURES (1) - Overview

The following assessments and procedures schedule will be will be followed during the course of the study.

Assessment and procedures Schedule – DOLAB II

| Procedure | Screening | Baseline | Bi-Weekly Contact | Post-  intervention |
| --- | --- | --- | --- | --- |
|  |  | Day 7 +/- 2 d |  | Day 112 +/- 2d |
| Informed Consent | X |  |  |  |
| Prior & Concomitant Medications | X | X |  | X |
| Inclusion/Exclusion | X |  |  |  |
| Finger Prick (optional) |  | X |  | X |
| BAS 3 Reading Test (C) |  | X |  | X |
| BAS II Reading Test (C) |  | X |  | X |
| BAS II Working Memory Digit Span (C) |  | X |  | X |
| Conners Teacher Ratings (T) |  | X |  | X |
| Connors Parent Ratings (P) |  | X |  | X |
| Demographics (P) |  | X |  |  |
| Randomisation |  | X |  |  |
| Prediction Test Group (T, C, P) |  |  |  | X |
| Barkley Side Effects Rating Scale |  |  |  | X |
| Adverse Events |  |  | X | X |
| Capsule Compliance |  |  | X | X |
| Illness Tracking Questions |  |  | X | X |

Recruitment will be carried out over two years. There will be two assessment points for children: i) screening/baseline, and ii) post-intervention for children who are randomized to treatment.

This section will outline the overall study schedule, the measures that will be administered at each of the assessment points (and by whom), how they will be performed and what will be done with these data.

The following section will provide further details of each of the assessments used.

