## Bi-weekly

Parents will be telephoned to check on any absences their child may have had from school, due to illness, once a fortnight. Details will be logged about any such illnesses, for example upper respiratory illness (nose and throat), lower respiratory illness (lungs, chest), ear infection, vomiting, diarrhea, rash or ectopy, food allergy, asthma, fever, lower GI (gastritis).

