### Side effects scale

Side effects will be measured post-intervention in all randomised children using the Barkley Side Effects Rating Scale (SERS) (Barkley 1990). This scale was designed for use in studies of stimulant medication for ADHD-type symptoms. Based on our own and others’ previous studies, negative side effects are not expected from supplementation with DHA Omega-3, but we are conscious that few studies specifically ask about these effects, so the use of this scale will redress that omission.

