# ADVERSE EVENT COLLECTION

Parents will be telephoned to check on any absences their child may have had from school, due to illness, once a fortnight. Details will be logged about any such illnesses, for example upper respiratory illness (nose and throat), lower respiratory illness (lungs, chest), ear infection, vomiting, diarrhoea, rash or ectopy, food allergy, asthma, fever, lower GI (gastritis). During this telephone call parents will be asked about any adverse events which may have occurred.

Definition of Serious Adverse Events

A serious adverse event is any untoward medical occurrence that:

- Results in death,
- Is life-threatening,

NOTE: The term "life-threatening" in the definition of "serious" refers to an event in which the participant was at risk of death at the time of the event; it does not refer to an event which hypothetically might have caused death if it were more severe.

- Requires inpatient hospitalisation or prolongation of existing hospitalisation,
- Results in persistent or significant disability/incapacity, or
- Is a congenital anomaly/birth defect.
- Other important medical events.*

*Other events that may not result in death, are not life threatening, or do not require hospitalisation, may be considered a serious adverse event when, based upon appropriate medical judgement, the event may jeopardise the participant and may require medical or surgical intervention to prevent one of the outcomes listed above.

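### The protocol relies on a scale designed for stimulant medication to fill a gap in asking about DHA side effects, and does not show that it covers effects plausible for a daily oil capsule

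*Protocol*

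**What the plan says.** The protocol's section on the side effects scale has the Barkley scale given after the intervention to all randomised children. On its origin it states: "This scale was designed for use in studies of stimulant medication for ADHD-type symptoms". It does not expect harm from DHA, but it explains the choice by adding that "we are conscious that few studies specifically ask about these effects, so the use of this scale will redress that omission". The Post-intervention section lists the scale among the forms that parents return by post.

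Other safety information is collected as well:

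- **Fortnightly telephone call.** "Parents will be telephoned to check on any absences their child may have had from school, due to illness, once a fortnight". The illnesses behind those absences are logged. The examples given in the Adverse Event Collection section include "ear infection, vomiting, diarrhoea, rash or ectopy, food allergy, asthma, fever, lower GI (gastritis".
- **General enquiry in the same call.** "During this telephone call parents will be asked about any adverse events which may have occurred".
- **Health questionnaire.** Parents complete one at baseline and again after the intervention. Its content is not given.

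No section adapts the Barkley scale to this product or names a supplementary list of side-effect items.

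**The concern.** The section on the scale identifies a weakness in the field, namely that few studies ask specifically about side effects, and offers the Barkley scale as the remedy. A remedy of that kind works only if the questions match the effects that the product could plausibly cause. By the protocol's own account, the scale was written for a different class of treatment. The product here is three flavoured oil capsules a day, for which digestive, taste, skin or swallowing complaints are the natural things to ask about. The protocol does not say whether the scale asks about them.

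What is at stake is the trial's description of tolerability. If mild capsule effects are not put to every parent in the same words, their frequency in each arm depends on what parents think to mention. Such effects also bear on two things that the protocol does record: stopping the intervention because of side effects, and the guesses of treatment group used to check blinding. Fixed items would help to explain both. Items missing from the form cannot be recovered later by a statistical analysis plan, so the protocol and its forms are the place to settle this.

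**Working it through.** The protocol states no safety hypothesis, event rate or margin, and its sample size statement concerns reading change scores only. There is therefore no figure to reproduce and no calculation that rests on the document. The check is a comparison of sections, asking of each source whether it commits the trial to a fixed question on mild capsule effects for every randomised child.

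1. **Barkley scale** (Side effects scale; schedule table; Post-intervention). It is structured and put to the parents of all randomised children. The schedule row, "Barkley Side Effects Rating Scale | | | | X", has its single mark in the post-intervention column. The stated design purpose is stimulant studies. The items are not reproduced, so coverage of oil-capsule effects is neither shown nor excluded.

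2. **Adverse-event question** (Adverse Event Collection; schedule table). The schedule row, "Adverse Events | | | X | X", marks the bi-weekly and post-intervention columns. Over 16 weeks a fortnightly call gives about 16 / 2 = 8 enquiries. The question is actively asked and is not limited to absences. As described, however, it is general: it names no effects, and specific enquiry is what the section on the scale says has been lacking.

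3. **Illness log** (Bi-weekly; Adverse Event Collection). Its examples include digestive, skin and allergic conditions. It is tied to school absence because of illness. A child with belching, an aftertaste, a mild stomach ache or loose stools who still attends school does not enter it.

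4. **Health questionnaire** (Baseline; Post-intervention). It is structured and completed by parents at both time points. Its content is not shown, so it may or may not contain relevant items.

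Sources 1 and 4 are structured, but their coverage is not shown. Source 2 reaches everyone but is not specific. Source 3 names relevant conditions but depends on absence. None of the four, as written, commits the trial to fixed questions for every parent on milder capsule effects. The design purpose stated in source 1 and the role assigned to it in the same section are left unreconciled.

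**The case against.** The strongest reply is that an established, published scale used beside repeated active enquiry is a defensible choice, openly disclosed, and that a different checklist is a matter of preference. Much of this stands, and it limits the point in four ways.

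- **A reader might infer that the scale misses oil-capsule effects.** The document cannot support that. The items are not reproduced, and a scale built for one drug class may still ask about digestive or other general symptoms. What can be said is that coverage is not shown.
- **A reader might infer that the safety assessment rests on this scale alone.** It does not. Adverse events are asked about at each fortnightly call and again after the intervention, and the illness examples are introduced as examples, so the absence of taste or reflux from them shows little. The health questionnaire is a further source.
- **A reader might infer that the protocol will treat a clean scale result as proof of safety.** It does not say so. The Potential Risks section rests on regulatory status and earlier clinical studies.
- **A reader might want a figure for lost power to detect a side effect.** The protocol gives no event rates or capture rates. The placebo is also three oil capsules a day, with a matching shell, flavouring and masker, so many capsule effects would be expected in both arms. Any assumed difference between arms would have no basis in the document.

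The reply does not remove the mismatch within the section on the scale. The protocol itself sets specific enquiry as the aim, and neither a general question nor an absence log is specific enquiry. Matching the placebo does not make fixed items pointless either: the absolute frequency of shared effects still describes how tolerable daily capsules are for children.

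**Conclusion.** The concern holds in a limited form. The protocol assigns the Barkley scale a task for which, on its own account, the scale was not designed, and it neither justifies the choice for this product nor supplements it. The remaining collection does not guarantee that every parent is asked fixed questions about mild capsule effects.

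Severity is minor. The primary outcomes, the randomisation and the sample size are unaffected, and serious or absence-causing events have other routes into the record. The consequence is a weaker description of tolerability, which cannot be quantified from the document. The conclusion assumes that neither the Barkley items nor the health questionnaire, once inspected, already covers these effects in full. If they do, a sentence in the protocol saying so would be enough.

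**What to change.** Keep the Barkley scale. Before changing anything, compare its items and those of the health questionnaire with a short list of effects plausible for an oil capsule, for example nausea, belching or aftertaste, abdominal pain, loose stools, skin reaction and difficulty swallowing the capsules. For any that are not covered, add a fixed yes/no and severity item to the post-intervention parent form. Ask it for all randomised children, whether or not they missed school, and report the answers by arm beside the adverse-event data.

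Amend the section on the side effects scale to state that the scale was not designed for this product and is supplemented by these items. Do not state that it covers stimulant-type effects only, since its content is not shown.

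The cost is at most about six lines on a form pack that parents already receive, one further table and one amended sentence. The downside is a slightly longer form and more minor events reported in both arms. Nothing changes in the intervention or the efficacy outcomes.

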### Attendance

Attendance will be measured by way of school records pre and post-intervention. Parents will also be contacted fortnightly in order to establish any absences and the nature of any illnesses during the course of trial. We will make a distinction between absences due to illness and those due to, for example, holidays during term-time.

# STATISTICAL CONSIDERATIONS

A separate and full statistical analysis plan will be developed prior to the analysis of the study. The protocol will be discussed and agreed by the Trial Steering Committee (see below).

##

## Method of Randomisation

Randomisation of children will be conducted using dedicated computer software. The randomisation programme will include a minimisation algorithm to ensure balanced allocation of participants across the treatment groups by sex and school (to allow for any sociodemographic/school differences).

## Outcome Measures

### Primary outcome

- Can supplementation with DHA Omega-3 improve child behaviour and learning in underachieving children in year groups 3, 4 and 5 (who are generally aged 7-9 years)? Outcomes assessed will include reading performance, working memory and ADHD-type symptoms (inattention, hyperactivity, impulsivity) as rated by parents.

### Secondary outcomes

- Can supplementation with DHA Omega-3 improve child ADHD-type symptoms (inattention, hyperactivity, impulsivity) as rated by teachers?
- Do children’s levels of DHA Omega-3 or related fatty acids (assess objectively via a pinprick blood sample) predict their learning or behaviour?
- Are any changes in behaviour or cognitive performance associated with changes in blood fatty acid status?
- Sickness measures, school days missed.

## Sample Size

Power calculations (using post-intervention standardised reading change scores on the bottom 20^th^ centile readers from the DOLAB study) indicates that an n of 400 (199 per treatment arm) is an appropriate target when desired power is set at .05 alpha level.

## Analysis Plan

The study will be analysed and reported following the ‘CONSORT’ guidelines (Consolidated Standard of Reporting Trials) (Moher, 2001).

On completion of the study, data from all randomised children will be analysed on an intention to treat basis.

All analyses will be pre-specified in detail in the statistical analysis plan to be drawn up and agreed by the Trial Steering Committee, but will include subgroup analyses for the bottom 10% readers in line with exploratory findings (Richardson et al 2012). Missing data will be handled using various imputation methods. The robustness of the complete case analysis will be assessed (with a worst and best case) sensitivity analysis, however these will be informed by data collected on the reasons for any missing data.

# ADVERSE EVENT COLLECTION

Parents will be telephoned to check on any absences their child may have had from school, due to illness, once a fortnight. Details will be logged about any such illnesses, for example upper respiratory illness (nose and throat), lower respiratory illness (lungs, chest), ear infection, vomiting, diarrhoea, rash or ectopy, food allergy, asthma, fever, lower GI (gastritis). During this telephone call parents will be asked about any adverse events which may have occurred.

Definition of Serious Adverse Events

A serious adverse event is any untoward medical occurrence that:

- Results in death,
- Is life-threatening,

NOTE: The term "life-threatening" in the definition of "serious" refers to an event in which the participant was at risk of death at the time of the event; it does not refer to an event which hypothetically might have caused death if it were more severe.

- Requires inpatient hospitalisation or prolongation of existing hospitalisation,
- Results in persistent or significant disability/incapacity, or
- Is a congenital anomaly/birth defect.
- Other important medical events.*

*Other events that may not result in death, are not life threatening, or do not require hospitalisation, may be considered a serious adverse event when, based upon appropriate medical judgement, the event may jeopardise the participant and may require medical or surgical intervention to prevent one of the outcomes listed above.

## Reporting Procedures for Serious Adverse Events

A serious adverse event (SAE) occurring to participant should be reported to the REC that gave a favourable opinion of the study where in the opinion of the Chief Investigator the event was: ‘related’ – that is, it resulted from administration of any of the research procedures; and ‘unexpected’ – that is, the type of event is not listed in the protocol as an expected occurrence. Reports of related and unexpected SAEs should be submitted within 15 days of the Chief Investigator becoming aware of the event, using the NRES [report of serious adverse event](http://www.nres.npsa.nhs.uk/docs/forms/Safety_Report_Form_(non-CTIMPs).doc) form (see IRAS/NRES website).

The Chief Investigator shall inform DSM of any SAEs in relation to the use of the Study Product within a maximum of 24 hours after the University is made aware of the SAE. The SAE reports will not contain any information which could identify any study participant. On completion of the study, the Chief Investigator shall provide DSM will a list of SAE’s occurring throughout the study period.

## Potential Risks and Benefits of Omega 3s

### Potential Risks

None are known. According to the US FDA, 3g per day of EPA + DHA is generally regarded as safe (GRAS). This study will use only 600mg.

Clinical studies of Omega-3 supplementation in humans (adult and child volunteers and patients of both sexes and all ages) have not shown any consistent or serious short or long-term adverse side-effects.

DSM Nutritional Products’ DHA-S is already widely used in human nutrition as it is used in adult, maternal and child supplements as well as a variety of food and beverage products. The FDA considers both DHA-S and corn/soy oil to be “highly refined oils” that are not associated with allergic reactions.^[[3]](#footnote-3)^

### Potential Benefits

Clearly, benefits can never be guaranteed for individual participants in any research trial, but average intakes of DHA in the UK and other developed countries are widely acknowledged to be suboptimal for general health (Hibbeln *et al* 2006). Adequate supplies of DHA are essential for optimal development and functioning of the brain and nervous system (particularly for vision), and for cardiovascular and immune health.

As noted above, preliminary RCT evidence from studies of healthy children has already shown improvements in attention, concentration and behaviour, and benefits for literacy skills. The aim of this study is to confirm and extend these findings.

# ETHICAL CONSIDERATIONS

## Ethical considerations

The study will abide by the principles of the Declaration of Helsinki and subsequent revisions. We consider the specific ethical issues relating to participation in this study to be:

- Taking a placebo (dummy) treatment or the active (DHA Omega-3) treatment.

There is no single, 'gold standard' treatment that is used to combat scholastic underachievement and/or behaviour problems in children. Those drugs that are sometimes prescribed for behaviour problems associated with ADHD have obvious and unpleasant side-effects that would make blinding difficult in any case, but more fundamentally, they are not an appropriate intervention for normal children who are simply underperforming at school. Placebo is therefore an appropriate comparator because (a) there is no standard treatment and (b) double-blinding enables the true treatment effect of DHA Omega-3 to be investigated.

- Case Report Forms and Assessments in English only

To provide appropriate translations of all study documentation and assessments would require checks and validations of language, as well as a comprehensive review of cultural and linguistic influences on the study measures. The latter include age-standardised tests of literacy skills, which are likely to be affected by the primary language spoken. We unfortunately do not have the resources to fulfil these standards adequately and therefore must limit study entry to children with English as a first language.

## Ethical Approval

No study procedures will take place until full approval has been given by an NHS ethics committee.

## Informed Consent Process

Informed consent is a process initiated prior to an individual agreeing to participate in a study and continues throughout the individual’s participation. Informed consent is required for all individuals participating in coordinated studies. In obtaining and documenting informed consent, the investigators will comply with applicable regulatory requirements and adhere to the ethical principles that have their origin in the Declaration of Helsinki.

# STUDY MONITORING

## Site Monitoring

### Direct Access to Data

Site monitoring may be deemed to be necessary as a result of central data checks. In order to perform their role effectively, the trial coordinator and others involved in Quality Assurance and Inspection may need direct access to primary data, eg. school records, relevant medical reports etc. Since this affects the participant’s confidentiality, this fact is included on the Participant Information Sheet and Informed Consent Form.

### Confidentiality

Individual participant medical information obtained as a result of this study is considered confidential, and disclosure to third parties is prohibited with the exceptions noted below.

Electronic and paper record forms will be labeled with participant’s unique trial registration and/or randomisation number. Verification of appropriate informed consent will be enabled by the provision of copies of participants’ signed informed consent/assent forms being supplied to the schools.

The Centre for Evidence Based Intervention (CEBI) will preserve the confidentiality of participants taking part in the study and The University of Oxford is registered under the Data Protection Act. Access to anonymised data may be given to authorized individuals from both the University of Oxford and DSM Nutritional Products for the purposes of monitoring and/or audit.

### Quality Assurance and Quality Control of Data

This study will undergo a risk assessment, the outcome of which is likely to indicate that it is a low risk study. As such, site visits will be conducted and source data reviewed if indicated to be required as a result of central monitoring processes. To this end:

- The Investigators, the Trial Coordinator and other staff will attend the launch meetings for key staff from participating schools, which will incorporate elements of study-specific training necessary to fulfill protocol requirements.
- The Trial Coordinator will verify that appropriate approvals are in place prior to initiation of a school, and to check that the relevant personnel have attended study-specific training.
- The Trial Coordinator will check safety and compliance reporting rates between centres.
- The Trial Coordinator will monitor screening, recruitment and drop-out rates between schools.
- The Trial Coordinator will conduct data entry consistency checks and follow-up data queries.
- Independent oversight of the study will be provided by the Trial Steering Committee.

##

